In contrast, substantial evidence has been presented on the relationship between MM and functional impairment (3, 16, 17). On the one hand, it has been found that the accumulation of chronic diseases may lead to functional impairment (16, 18). On the other, functional decline has been found to be associated with a higher risk of developing multiple chronic diseases, consequently increasing the severity and MM burden (3, 19). It has also been suggested that functional decline in older hospitalized patients may be a stronger predictor of poor outcomes than MM (3, 17, 20–22). Despite all the evidence, it is still unclear how these factors interact with one another and how polypharmacy may impact both.

Several studies have provided solid evidence that it is not merely by accident that chronic diseases may coexist (23–26). Both clinical experience and epidemiological research suggests that diseases often co-occur in an individual according to specific patterns (27, 28). However, no consensus has been reached on how these classifications can be applied to an operational definition to measure MM.

Several attempts have been made to develop a concise measure of MM and quantify its severity (29). However, a dearth of knowledge regarding its pathophysiology prevented the estimation of its severity in terms of outcomes. In order to bridge this gap, weighted disease measures, such as the Charlson Comorbidity Index (30), have been used to define the impact of multiple combinations of health/disease conditions on multiple outcomes, including mortality, quality of life, and resource utilization. However, the majority of studies aimed at estimating the risk of death in patients with MM by utilizing multiple comorbidity indexes indicated a high risk of bias (29).

In this context, a series of circulating physiological markers, including dehydroepiandrosterone sulfate (DHEAS), interleukin 6 (IL-6), C-reactive protein (CRP), cystatin C (Cyst-C), Alpha-2-macroglobulin (A2M), and soluble receptor for advanced glycation end-products (sRAGE), have been found to be associated with several age-related diseases and MM, indicating a potential clinical application for addressing patients with a higher risk of poor outcomes (31–34).

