We hypothesize that a comprehensive characterization of patients with MM, by integrating the assessment of selected circulating and epigenetic biomarkers with the medical history, in addition to an assessment of functional capacity, could improve the long-term mortality prediction of these patients.

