## Materials and methods

### Study design

This monocentric retrospective observational study was conducted as part of a project funded by the Italian Ministry of Health (Grant No. GR-2019-12368606) titled “imProving the pROgnostic value of MultimOrbidity through the inTegration of selected biomarkErs to the comprehensive geRiatric Assessment (PROMOTERA).”

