#### CGA

CGA was conducted at admission and discharge using the validated interRAI Minimum Dataset for Acute Care (MDS-AC) (51), encompassing identification information, demographic data, functional state assessment, number and type of diagnoses, and number and type of medications, treatments, and procedures (50). Functional status was evaluated on the basis of several dimensions: the number of impaired basic and instrumental activities of daily living (BADL and IADL) (48, 52, 53) as a measure of functional status; the cognitive performance scale (CPS) as a measure of cognitive function; sensory functioning (hearing and vision); history of falls; pressure sores and skin conditions; pain; delirium, and behavioral changes; nutritional status and oral health; urinary incontinence; and, recent weight loss.

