In order to reduce the complexity of MM, a dimensionality reduction approach will be performed by clustering patients into a few groups on the basis of the most frequent diagnoses at baseline for each stratum in order to obtain a classification of patients according to an MM pattern. The risk analysis will be repeated for each MM pattern. The association between the epigenetic clock and MM patterns will be determined by means of a Generalized Linear Model. Multiple adjusted models will be developed to consider each possible covariate that could influence the significance of the results and to identify independent variables linked to primary and secondary outcomes. Survival analysis with Kaplan Meier estimates will be performed to assess and compare survival over time among the clusters (Log-Rank test). Cox proportional hazards models will be used to assess and compare survival-time outcomes in each cluster in the presence of possible confounders. Several network medicine-based approaches will be developed in order to build the Human Interactomes and Disease Networks (58). Finally, we will investigate the additive effect of the epigenetic clock on the predictive ability of MM patterns. Changes in Harrell's C and the categorical Net Reclassification Index (NRI) will be calculated with 1,000 bootstrap samples to estimate the 95% CI. A two-tailed *p*-value of < 0.05 will be considered statistically significant. The Bonferroni correction for multiple comparisons will be applied to control for the risk of false-positive results. Statistical analyses will be conducted using the Stata 15.1 Software Package for Windows (Stata Corp, College Station, TX).

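### The added-value analysis puts the epigenetic clock on top of diagnosis clusters only; its stated base names no age, sex, function or cognition, and no change metric is tied to the plasma proteins

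*Protocol article*

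**What the plan says.** **What is promised.** The project title is "imProving the pROgnostic value of MultimOrbidity through the inTegration of selected biomarkErs to the comprehensive geRiatric Assessment". The hypothesis at the end of the Introduction is that long-term mortality prediction could improve "by integrating the assessment of selected circulating and epigenetic biomarkers with the medical history, in addition to an assessment of functional capacity". Phase VI expects better prognosis from combining diagnoses, comprehensive geriatric assessment (CGA), routine laboratory data, epigenetics and plasma proteins.

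**What is measured as an increment.** In Statistical analysis, one comparison is called additive: "Finally, we will investigate the additive effect of the epigenetic clock on the predictive ability of MM patterns". The next sentence supplies the metrics: "Changes in Harrell's C and the categorical Net Reclassification Index (NRI) will be calculated with 1,000 bootstrap samples to estimate the 95% CI". The MM patterns come from "clustering patients into a few groups on the basis of the most frequent diagnoses at baseline".

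**What the CGA holds.** The CGA section describes it as "encompassing identification information, demographic data, functional state assessment, number and type of diagnoses", followed by medications, treatments and procedures. It then lists basic and instrumental ADL, and CPS for cognition.

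**What is planned for the proteins.** They are to be assessed in relation to outcomes (Secondary objectives), selected by association in stage 1 (Phase IVb), validated in stage 2 (Phase V) and integrated with the other data (Phase VI). Statistical analysis does not name them.

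**The concern.** A change in C or an NRI measures what a marker adds to a particular base model, so the base decides what the result means. Here the named base is a diagnosis grouping, while the hypothesis concerns biomarkers used alongside history and functional capacity.

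The article itself gives reasons to expect function to matter. The Introduction says that "functional decline in older hospitalized patients may be a stronger predictor of poor outcomes than MM". It also cites epigenetic clocks as prognostic for functional impairment and frailty, and the Secondary objectives plan to relate the clock to ADL and CPS. Both links, clock to function and function to death, are thus in the text. If function is left out of the base, the clock can take credit for information that a bedside score already supplies.

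Age matters too. Δage is epigenetic age minus chronological age, so it is in general correlated with age. A base without age lets the clock gain or lose for that reason alone.

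At stake is the use of the result: Strengths and limitations says the study will recommend bringing several biomarkers into clinical settings.

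**Working it through.** **1. The plan's own figures.** The plan gives no figure for added value. Its sample-size inputs give the expected deaths. Exponential survival with a median of 6.2 years over 10 years gives 1 − 0.5^(10/6.2) = 0.673, or 0.673 × 1,070 = 720 deaths. With half the cohort at HR 1.23 (a 1:1 split, assumed), the average is (0.673 + 0.747)/2 = 0.710, or 760 deaths. Schoenfeld's formula needs 733 events, so 733/0.710 ≈ 1,033 patients. Freedman's needs 738, so about 1,040. Both are close to 1,070, and the sample size is not at issue.

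**2. Assumed inputs, not from the documents.** The clock has no effect on death once function is known. Function has HR 1.3 or 1.5 per SD. The clock-function correlation ρ is 0.1, 0.2 or 0.3. The clock is taken as available for all 1,070 patients.

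**3. Analytic check.** Over a base without function, the apparent log HR per SD of clock is about ρ × ln(HR of function), and z is that times √deaths. The chance of p < 0.05 is Φ(z − 1.96) + Φ(−z − 1.96). Example: 0.3 × ln 1.5 × √760 = 0.1216 × 27.57 = 3.35, giving 92%.

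**4. Simulation.** 300 Cox studies per setting, n = 1,070, four MM patterns, 67% deaths.

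| Function HR | ρ | z (760 deaths) | Analytic | Simulated, base = MM patterns |
|---|---|---|---|---|
| 1.3 | 0.1 | 0.72 | 11% | 11% |
| 1.3 | 0.2 | 1.45 | 30% | 25% |
| 1.3 | 0.3 | 2.17 | 58% | 51% |
| 1.5 | 0.1 | 1.12 | 20% | 15% |
| 1.5 | 0.2 | 2.24 | 61% | 52% |
| 1.5 | 0.3 | 3.35 | 92% | 87% |

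With function in the base, the simulated rate is 5% throughout. Using 720 deaths instead of 760 changes little: the last row becomes z = 3.26 and 90%.

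**5. The planned metric, change in C.** A second simulation (60 studies per setting) let disability depend on age and pattern. Mean gain in C from the clock, function HR 1.5:

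| ρ | MM patterns | + age | + age + disability |
|---|---|---|---|
| 0.1 | 0.0038 | 0.0005 | 0.0002 |
| 0.2 | 0.0097 | 0.0017 | 0.0005 |
| 0.3 | 0.0155 | 0.0033 | 0.0002 |

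A third simulation used the six settings of step 4 (100 studies each, age independent of function). The gain was 0.003 to 0.011 over patterns alone and 0.0004 to 0.003 with age added.

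The apparent gain over diagnosis clusters is small in C. It shrinks with age in the base and all but disappears with function.

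**The case against.** **Other analyses may include function.** The main Cox model is to be corrected for age, gender and clinical, functional or biological data, with Harrell's C estimated. It is then repeated adding single CpGs. Further adjusted models are planned. This stands in part: a clock that only mirrors disability could be exposed there. But the "or" leaves open whether function enters, no change in C or NRI is tied to that model, and an adjusted hazard ratio does not measure added predictive value.

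**Silence is not exclusion.** The article does not say that function is left out, and the unseen full protocol or SAP may list covariates. This limits the point to what is named. The article does, however, fix the comparison and its metrics, and the base it names is a diagnosis grouping.

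**Clock over MM patterns answers a stated aim.** This stands. Aim (ii) in the Abstract is better prognostic accuracy of MM patterns, and the primary objective is the clock's performance. The comparison belongs in the plan.

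**The size is assumed.** This also stands. The correlations and function HRs are not document figures, and zero independent clock effect is the worst case. Step 4 counts Cox p-values, not the planned C and NRI. If Bonferroni covered three clocks (α = 0.05/3, an assumed family), the rate over patterns alone in the third simulation falls from 8–82% to 3–69%.

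**Conclusion.** The point holds for the added-value analysis. Its named base is narrower than the hypothesis, and no change metric is tied to the proteins. A clock that largely mirrors disability can appear to add prognostic value: Cox p < 0.05 in roughly 11% to 87% of simulated studies under the assumptions above, with small gains in C.

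A reader might infer more than the documents support:

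- *That the CGA is absent from the base.* Diagnoses are part of the CGA and form the MM patterns. What goes unnamed is mainly function and cognition.
- *That such a clock will appear to add value.* At a correlation of 0.1, only 11% to 15% of simulated studies showed it.
- *That the proteins are never tested, or that the study cannot test its hypothesis.* Phase VI integrates them with clinical and functional data, Harrell's C is planned for exposure variables, and the Discussion plans a combined algorithm. What is lacking is a stated comparison with and without the proteins.

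**What to change.** 1. Keep the comparison of the clock over MM patterns for aim (ii), but put age and sex in its base.
2. Add the same change-in-C and NRI analysis over a base of age, sex, MM pattern, ADL and CPS, in three versions: adding the clock Δage, adding the validated plasma proteins, and adding both.
3. Name the third version (both classes over the full base) as the test of the hypothesis in the Introduction.

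The cost is wording and a few extra model fits, with the metrics and bootstrap already planned. ADL and CPS come from the existing Reportage data, and the biomarkers are to be measured anyway. The added comparisons fall within the Bonferroni family, and the clock's apparent gain will be smaller.

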The PROMOTERA study aims to identify promising biomarkers of healthspan and mortality, such as selected circulating proteins and several DNA methylation biomarkers in the plasma and blood samples of hospitalized older patients recruited by the Reportage project (Trial registration number: NCT01397682; July 19, 2011). The Reportage project is (50) an ongoing prospective observational study involving older patients consecutively admitted to acute care wards in INRCA research hospitals located in the Italian cities of Ancona, Fermo, Cosenza, and Casatenovo. The project began in September 2011 with the aim of creating a large data repository on demographics, comprehensive geriatric assessments, clinical and diagnostic information, and molecular and biological data on older adults receiving acute care. This study included patients who were recruited until 2019. Potential participants were screened for eligibility after they were provided with information describing the study. Eligibility criteria included: age ≥ 65 years, admission to one of the INRCA research hospitals, and written informed consent. In the case of a participant's cognitive decline or impaired judgment, a proxy (relative or caregiver) was requested to give their additional consent. The absence of informed consent from the patient or caregiver (50) resulted in the participant's exclusion from the study. Baseline data were collected for each patient within the first 24 h of hospital admission. Baseline data were incorporated into a minimum data set comprising demographic information, multidimensional geriatric assessment data, clinical, biological, and diagnostic information routinely collected during hospitalization, also utilizing the interRAI Acute Care Instrument (51). Moreover, the Reportage dataset contained information on drug intake (prior to admission, during hospitalization, and at discharge) and diagnostic and treatment procedures performed during hospitalization (including information from X-rays, computerized tomography, ultrasounds, electrocardiograms, magnetic resonance imaging, etc.). The multidimensional geriatric assessment was repeated within 24 h prior to discharge. Blood samples were taken within 24 h of admission and stored at −80°C. A separate and detailed data sheet was used to collect data regarding *ad hoc* investigations to identify biological markers.

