### Outcome variables

#### Overall mortality

Mortality data include the date, place, and causes of death (when available). Up to 10 years' information on survival status (i.e., dead or alive) will be obtained from the Marche Region's administrative database.

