### Sample size

The sample size was calculated on the basis of the primary objective (the association between the epigenetic clocks' Δage and mortality). For this reason, we planned to include 1,070 samples of individuals from the Reportage Project. This sample was obtained by setting α = 0.05, β = 0.2, and using a Hazard ratio = 1.23, a 10-year follow-up period, and a median survival time of 6.2 years for patients whose Δage was not expected to increase. This sample size is also in line with other study populations in which the prognostic value of several epigenetic clocks were assessed (36). This sample will enable the detection of significant associations between epigenetic clock Δage and mortality during the 10-year follow-up period.

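### The categorical NRI in its standard form needs a known status at a fixed horizon, which entry up to 2019 cannot supply at 10 years; a censoring-aware form and a clear follow-up rule are needed

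*Protocol article*

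**What the plan says.** All places are in the Protocol article.

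- **Statistical analysis** plans the added-value comparison as follows: "Changes in Harrell's C and the categorical Net Reclassification Index (NRI) will be calculated with 1,000 bootstrap samples to estimate the 95% CI". It gives no horizon, risk categories or rule for censored patients for this index. The survival model in the same section concerns 10-year survival.
- **Study design** sets the entry window: "The project began in September 2011" and "This study included patients who were recruited until 2019".
- **Overall mortality** describes the outcome data: "Up to 10 years' information on survival status (i.e., dead or alive) will be obtained" from the regional administrative database. No data cut-off date is given. The same section, and Phase I, say that the date of death is collected.
- **Phase II: Patient selection** makes it an inclusion criterion that death, hospitalization, clinical and other information be available from baseline through 10 years.
- **Sample size** works from these figures: "using a Hazard ratio = 1.23, a 10-year follow-up period, and a median survival time of 6.2 years".
- **Strengths and limitations** expects fewer censored observations than in a community cohort, not none, yet also describes the patients as monitored for 10 years.

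**The concern.** The categorical NRI counts upward and downward moves between risk groups, separately among patients who had the event by the horizon and patients who did not. A patient alive at data cut-off after six years is neither a 10-year death nor a 10-year survivor. The Cox model and Harrell's C can use such a patient. The standard NRI cannot, without an added rule.

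A patient entered in 2019 reaches 10 years only in 2029, so the problem touches a large share of the cohort at any cut-off near this project. If these patients were placed with the survivors, future deaths would enter the non-event group and shrink the non-event part of the index. The bootstrap would reproduce that bias in its interval, not remove it. At stake is one of the two measures used to judge whether the clock improves prediction beyond multimorbidity patterns, which is the study's stated hypothesis.

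**Working it through.** **1. The plan's own sample size.** Inputs: HR 1.23, two-sided α 0.05, power 0.80, median 6.2 years, 10 years of follow-up; a 1:1 split is assumed.

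- Hazard λ = ln 2 / 6.2 = 0.1118 per year. Ten-year death probability: 1 − exp(−1.118) = 67.3% in the reference group, 74.7% at HR 1.23, mean 71.0%.
- Schoenfeld events: 4 × (1.960 + 0.842)² / (ln 1.23)² = 733. Dividing by 0.673 gives about 1,090.
- Freedman events: (1.960 + 0.842)² × (2.23 / 0.23)² = 738. Dividing by 0.710 gives about 1,040.

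Both are within 3% of 1,070, so the stated figure is reproduced. It assumes a full 10 years for everyone.

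**2. Patients with unknown 10-year status.** Assume uniform entry from September 2011 to date E (start or end of 2019), exponential survival as above, and data cut-off C. The unknown share is the integral of S(u) from u = C − E to the smaller of 10 and the longest follow-up, divided by the length of the entry window, averaged over the two hazards.

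Example, E = end 2019, C = end 2022 (window 8.33 years, u from 3 to 10):
- λ = 0.1118: (0.715 − 0.327) / 0.1118 / 8.33 = 41.7%.
- λ = 0.1375: (0.662 − 0.253) / 0.1375 / 8.33 = 35.7%.
- Mean 38.7%, or 414 of 1,070.
- Known 10-year survivors: (1.33 / 8.33) × 0.29 × 1,070 = about 50 (about 56 if entry ended at the start of 2019).
- Patients with under 10 years of potential follow-up: 7 / 8.33 = 84%. Of those unknown, 1 − (0.84 × 0.29) / 0.387 = 37% would still die by year 10.

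| Data cut-off | Unknown, entry to start / end of 2019 | Known 10-year survivors (entry to end 2019) | Deaths seen (same) | Deaths ÷ (deaths + known survivors) |
|---|---|---|---|---|
| early 2021 | 51% / 54% | 0 | 488 | 100% |
| mid-2022 | 39% / 43% | 31 | 579 | 95% |
| end 2022 | 35% / 39% | 50 | 606 | 92% |
| mid-2023 | 31% / 35% | 68 | 631 | 90% |
| end 2024 | 20% / 24% | 124 | 689 | 85% |
| end 2025 | 14% / 18% | 161 | 716 | 82% |

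**3. Effect on the index.** This was simulated. Beyond step 2 it assumes HR 1.23 per SD of the clock, an existing risk score, and chosen risk cut-points. For an end-2022 cut-off, a score with log-HR 0.7 per SD, and cut-points 50% and 80%:

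| Handling of unknowns | Event part | Non-event part | Total |
|---|---|---|---|
| Full 10-year status (truth) | 0.018 | 0.028 | 0.046 |
| Counted as survivors | 0.020 | 0.018 | 0.038 |
| Dropped | 0.020 | 0.029 | 0.049 |
| Kaplan-Meier form | 0.018 | 0.027 | 0.045 |

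Counting unknowns as survivors costs about one third of the non-event part. The event part rises slightly, so the total falls by 0.008 / 0.046 = 17%. With other cut-points and score strengths, the total falls by 18–19% at mid-2022 and 6–9% at end 2024. With a single 70% cut-point at mid-2022 the non-event part falls by more than a third in relative terms (0.0099 to 0.0033), but from a value below 0.01.

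Dropping the unknowns gives nearly the right value. Its weakness is precision: with about 50 known survivors, one patient changing category moves the non-event part by 1/50 = 0.02, against a true value of 0.028.

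**4. The selection criterion.** Read literally, Phase II leaves nobody unknown. A patient whose tenth year lies beyond the cut-off then qualifies only by having died. The last column of the table in step 2 is the resulting 10-year mortality among selectable patients: 85% to 95% for cut-offs from mid-2022 to end 2024, against the 71% implied by the sample-size inputs. Read loosely, the unknowns remain.

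**The case against.** The strongest reply is that the article states no error. A reader might infer that censored patients will be counted as survivors, because status is described as dead or alive. The documents do not support that. The phrase describes the registry variable and is not tied to the NRI; dates of death are collected; Cox, Kaplan-Meier and Harrell's C are all planned; and censoring is acknowledged. Categorical refers to risk groups and does not exclude a censoring-aware estimator. The choice of estimator is often left to an analysis plan, which is not shown here. The 10-year horizon for the index is inferred from the survival model and the sample size. The shares rest on an unstated cut-off, and the NRI figures on assumed cut-points and effect scale. There is also no decision rule attached to the index, and the change in Harrell's C stands beside it.

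All of this stands, and it limits the point to what the standard form of the index would do. It does not remove the point: the measure named does not, in its standard form, fit the follow-up that the article describes.

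A second reply is that Phase II guarantees complete information. As step 4 shows, that exchanges missing status for selection on death.

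**Conclusion.** The point holds as a mismatch between the named index and the follow-up structure, together with an unresolved conflict between entry to 2019, status for at most 10 years, and required information to 10 years. At a 10-year horizon, 14% to 54% of patients would lack a known status, about 40% at end-2022 and 25% at end-2024. If they were counted as survivors, the total index would fall by about 6% to 20% for cut-offs from mid-2022 to end 2024, with about a third off the non-event part at the earlier cut-offs when two risk cut-points are used. These sizes assume uniform entry, exponential survival with a 6.2-year median, and assumed risk categories.

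Two stronger readings should not be drawn. Excluding the unknowns is not shown to centre the interval on a materially wrong value; at end-2022 the cost is mainly the small number of survivors. Nor does the NRI problem reach the primary Cox test of Δage. That test is affected only if the Phase II criterion is applied literally and selects patients on their outcome. The change is worth making, but the effect is moderate and concerns the added-value analysis.

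**What to change.** 1. Reconcile Study design, Phase II and Overall mortality: follow each patient to death, 10 years or a stated administrative cut-off date, whichever comes first, and do not select on complete 10-year information.
2. In Statistical analysis, specify a categorical NRI with event and non-event proportions estimated by Kaplan-Meier within the moved-up and moved-down groups, or by inverse-probability-of-censoring weights, at one named horizon. Choose that horizon in view of how much follow-up the cut-off allows.
3. Report the event and non-event parts separately, and apply the 1,000 bootstrap samples to this estimator.

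The cost is a few sentences and slightly more programming. The downside is wider intervals at late horizons, where few patients remain under observation.

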### Phase V: Validation of biomarkers in the entire study population (stage 2)

The biomarkers selected in phases IVa and IVb will be validated on the remaining samples (75%, *n* = 798).

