### Phase VI: Association of overall biomarkers with primary and secondary outcomes

All the biomarkers validated in stage 2 will be integrated with the clinical, functional and biological data. Several biostatistical and bioinformatics analyses will be conducted to identify biomarker signatures that are strongly associated with primary and secondary outcomes.

The synergy between (a) detailed information about diagnoses for each individual patient, (b) a Comprehensive Geriatric Assessment (CGA), (c) routine laboratory data, (d) epigenetics data, and (e) plasma protein determination will improve the characterization of patients with MM, including the prognostic value for multiple outcomes such as overall mortality, re-hospitalization, and functional decline.

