### Statistical analysis

Baseline characteristics will be described using standard descriptive methods, such as summary statistics and frequency tables. Parametric and non-parametric statistical approaches (such as contingency table analysis, regression, and analysis of variance) will be used when appropriate.

Data pre-processing will be performed using the R package *minfi* (56) and a DNA methylation level will be summarized for each CpG site by calculating a “*beta*” value ranging from 0 to 100%. CpG probes will be treated as missing if the detection *P*-value > 0.01, and CpG sites with more than 5% missing data will be excluded from the analysis.

Epigenetic age will be calculated by multiplying beta values by the regression weights from Horvath [353 CpG sites (35)], Hannum [71 CpG sites (37)], and Levine [513 CpG sites (38)] to create the respective clocks. Delta age (Δage) will be defined as a simple subtraction of the chronological age from the epigenetic age using all the versions of the clock mentioned previously. In all cohorts, cell count predictions will be estimated from DNA methylation data using the Houseman method (57).

The determinants of overall 10-year survival will be calculated using Cox proportional hazards analysis including Δage as independent variables, and corrected for the following confounders: age, gender, clinical, functional, or biological data. The accuracy of exposure variables in predicting mortality will be estimated using Harrell's C-statistics. The same analyses will be repeated by adding the individual age-associated CpGs (one at once) to the Cox model. A two-stage approach will be adopted to validate individual CpG sites associated with mortality. Initially, all of the more than 850,000 methylation sites analyzed by the Illumina Infinium MethylationEPIC Array will be analyzed in a proportion π_sample_=25% of the study sample in stage 1 (*n* = 272), and the results of stage 1 will be used to select a proportion of these *M* CpG sites (Ω_marker_) for follow-up on the remaining sample in stage 2 (75%, n=798). The parameter Ω_marker_ will be selected on the basis of the corresponding *p*-values within the context of the survival analysis.

The validity of the estimated coefficients will be internally verified using a non-parametric bootstrapping resampling analysis with replacements.

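### Change in C and NRI are planned as apparent measures with no optimism correction: negligible for one published clock, material when several markers are added together

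*Protocol article*

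**What the plan says.** All references are to the protocol article.

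- **Statistical analysis, accuracy:** "The accuracy of exposure variables in predicting mortality will be estimated using Harrell's C-statistics". No held-out set or correction is named.
- **Statistical analysis, first bootstrap:** "The validity of the estimated coefficients will be internally verified using a non-parametric bootstrapping resampling analysis with replacements". Its object is the coefficients.
- **Statistical analysis, added value:** "Finally, we will investigate the additive effect of the epigenetic clock on the predictive ability of MM patterns". The next sentence gives the measures: "Changes in Harrell's C and the categorical Net Reclassification Index (NRI) will be calculated with 1,000 bootstrap samples to estimate the 95% CI". The object of this bootstrap is the interval. The type of interval is not stated.
- **Statistical analysis, clocks:** epigenetic age comes from published regression weights for three clocks (353, 71 and 513 CpG sites). These weights are not estimated in this cohort.
- **Phases IVa, IVb and V:** CpG sites and proteins are selected in a random 272 patients and validated in the remaining 798. The Phase V heading nevertheless reads "Validation of biomarkers in the entire study population (stage 2)".
- **Phase VI:** "All the biomarkers validated in stage 2 will be integrated with the clinical, functional and biological data". The patients in whom the integrated model's performance will be judged are not named.

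**The concern.** A model with extra fitted terms nearly always shows a higher C in the patients used to fit it, whether or not the terms carry information. A bootstrap that only forms an interval around that apparent gain leaves the bias in place. If the interval is a percentile interval of refitted changes, it adds the bias a second time, because each refit overfits its own resample.

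This matters because prediction is the study's purpose. The hypothesis is better long-term mortality prediction, the primary objective is the clock's predictive performance, and the Discussion looks ahead to a multicomponent algorithm for primary care. If several uninformative markers can show a gain with an interval above zero, the main conclusion could be reached without signal.

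**Working it through.** **1. The plan's own figures.** The article gives no expected change in C or NRI. Its sample size fixes n and the death rate, so that was reproduced first. Inputs from Sample size: two-sided alpha 0.05, power 0.80, hazard ratio 1.23, 10 years, median survival 6.2 years. Equal groups and exponential survival are assumed.

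- Reference 10-year death probability: 1 − exp(−ln 2 × 10/6.2) = 0.673. With the hazard multiplied by 1.23 it is 0.747. The mean is 0.710.
- Freedman events: 738. Patients: 738/0.710 = 1,039, within 3% of 1,070.

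So n = 1,070 with roughly 70% deaths is the right setting for the checks below.

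**2. Clocks with fixed external weights, pure noise.** The simulated base model holds age, sex and four MM clusters; only the Cox coefficients are fitted. Optimism = mean apparent change in C − mean change in new patients.

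| Noise clocks added | Apparent | New patients | Optimism |
|---|---|---|---|
| 1 | +0.0004 | −0.0004 | 0.0008 |
| 3 together | +0.0011 | −0.0011 | 0.0022 |

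Mean apparent NRI was +0.002 for one clock and +0.005 for three.

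**3. More markers fitted together.** Three clocks plus the six proteins under Protein variables make nine. The same definition of optimism gives about 0.007 for nine null markers.

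**4. Behaviour of the interval.** Share of null datasets in which the 95% percentile interval for change in C excluded zero (100 resamples each; three simulations with different base models):

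| Null markers | Share excluding zero |
|---|---|
| 1 | 1%, 1% and 5% |
| 3 | 7%, 10% and 18% |
| 9 | 86% |
| 10 | 88% |

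The cause shows in the nine-marker run. The mean apparent change was +0.0026, while the mean over resamples was +0.0051. A normal-based interval around the observed change excluded zero in only 1% of those datasets. The false-claim rate therefore depends on an interval type that the article does not state. The upward bias of the point estimate is there with either interval.

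**5. Selected CpGs.** The top 10 of 850,000 independent noise sites were chosen in 272 patients and then refitted:

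| Patients scored | Mean apparent change in C |
|---|---|
| The 272 discovery patients | +0.135 |
| All 1,070 | +0.0195 (NRI +0.09) |
| The 798 stage-2 patients | +0.005 |

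These figures assume that all 10 go forward with no stage-2 test. With a Bonferroni test in stage 2, a noise marker passed in 5% of runs and the mean change in all 1,070 was +0.0002. The 798 row is still positive because coefficients were refitted there, so the model has to be frozen, not only the marker list.

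**The case against.** The strongest reply is that the added-value sentence concerns the clock. Its weights are external, so nothing is selected in these patients, and for one clock the bias is too small to matter. This stands. So do three further points:

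- MM clusters are formed from baseline diagnoses and sit in both models, so they do not inflate the change.
- CpGs and proteins have a disjoint 272/798 split, and a Bonferroni correction is stated. Applied as a stage-2 gate, it removes nearly all of the selection inflation.
- The high rates in step 4 need nine or more null markers added jointly, and the article assigns no such number to the C and NRI comparison.

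A reader might infer that the planned clock analysis will make noise look predictive, or that the final algorithm will be scored in the patients who supplied its markers. The article supports neither. The clock is not selected here, Phase VI names no evaluation set, and the Phase V text limits validation to the 798 despite its heading.

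It can also be said that a condensed article leaves such detail to a fuller plan, which may specify a correction. That carries only part of the way. The article does not merely omit the point: it assigns each bootstrap a purpose, and neither purpose is optimism. The discovery split protects the choice of markers, but does not correct the C or NRI of a model later refitted with several of them.

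**Conclusion.** The point holds in limited form. As stated, accuracy and added value are apparent measures, and no bootstrap is used to correct them. The bias in C is about 0.001 or less for a single externally weighted clock, about 0.002 for three clocks and about 0.007 for nine jointly fitted null markers. It can be larger for selected CpGs if the discovery patients are scored and the stage-2 gate is weak or absent. In the multi-marker setting of Phase VI, noise can appear to improve prediction, and a percentile interval can exclude zero too often.

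The sizes assume independent null markers, complete 10-year follow-up, base-model effects chosen for the simulation, 10 CpGs carried forward and NRI cut-offs at risk tertiles. None of these is in the article. The direction does not depend on them; the amounts do. This should be changed, but it does not undermine the test of the clock's association with mortality.

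**What to change.** - Use the planned bootstrap to report optimism-corrected C and change in C. In each resample, repeat any marker selection and the fitting, score the refitted model in the resample and in the full cohort, and subtract the mean difference from the apparent value.
- For markers selected in stage 1, an alternative is to freeze the model in stage 1 and report its performance only in the 798 stage-2 patients.
- Do not use a percentile interval of refitted changes in C as the test of added value. State which interval will be used.
- Say in which patients the Phase VI model is judged.
- Reconcile the Phase V heading with its text, which limits validation to the remaining 798.

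The cost is more computing and a few lines of text, with no new data. The reported gain will be somewhat smaller.
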